## Abstract

*Background*. Oxaliplatin-induced peripheral neuropathy (OIPN) is one of the most common side effects of oxaliplatin, which can cause reduction and cessation of oxaliplatin-based chemotherapy and significantly affect patients' quality of life. However, no drug has got recognition to prevent or treat OIPN. Yiqi-Wenjing-Fang (YWF) is a joint name of Chinese medicine prescriptions with similar effects of tonifying qi and warming meridians, represented by Huangqi Guizhi Wuwu decoction (HGWD) and Danggui Sini decoction (DSD), both from “Treatise on Cold Pathogenic and Miscellaneous Diseases.” YWF granules, including HGWD granules and DSD granules, have been, respectively, demonstrated to be effective in preventing OIPN in previous small-sample observations. The purpose of this study is to enlarge the sample size for further evaluation of the preventive efficacy and safety of YWF granules on OIPN. *Methods and Analysis.* This study is a randomized, double-blind, placebo-controlled, and multicenter clinical trial. 360 postoperative patients with stage IIa-IIIc colorectal cancer will be randomly assigned into placebo-control group, intervention group I, and intervention group II, taking the mimetic granules of YWF as placebo, HGWD granules and DSD granules, respectively. All subjects will receive oxaliplatin-based chemotherapy regimen at the same time. EORTC QLQ-CIPN20 will be used to assess the degree of OIPN as the primary outcome measure. The grades of OIPN, quality of life, chemotherapeutic efficacy, and the number of completed chemotherapy cycles are selected as the secondary outcome measures. *Discussion*. Based on the condition of no recognized effective drugs in preventing OIPN, evidence-based medical study will be conducted for seeking a breakthrough in the field of Chinese herb medicine. This protocol could provide reliable and systemic research basis about the efficacy of YWF granules and the differentiation of two classical prescriptions of YWF on preventing OIPN objectively. *Trial Registration.* This study was registered at ClinicalTrials.gov on 26 December 2020 (ID: https://clinicaltrials.gov/ct2/show/NCT04690283).

## 1. Introduction

Oxaliplatin is a prime drug in the first-line standard chemotherapy regimens of colorectal cancer, included in mFOLFOX6, FOLFOX4, XELOX, and so on. The main side effect is dose-dependent neurotoxicity, namely, oxaliplatin-induced peripheral neuropathy (OIPN), which is the primary cause of reduction and cessation of platinum-based chemotherapy. Acute OIPN usually will develop in hours of oxaliplatin infusion and peaks 3 days later. About 90% of patients will undergo acute OIPN symptoms, characterized by abnormal sensations and muscle spasm of perioral region, tongue, throat, jaw, and limbs, triggered by cold stimulation. These acute symptoms can alleviate in a week or so but will recur as the next chemotherapy cycle comes subsequently [1, 2]. Chronic OIPN will gradually develop and aggravate after approximately 3 months of repeated administration, usually with more than 540 mg/m^2^ cumulative dose of oxaliplatin. Clinical manifestations of chronic OIPN are bilateral symmetric paresthesia, dysesthesia and/or allodynia of limbs (“glove-sock” distribution), disorder of fine motor coordination, sensory ataxia, and autonomic nervous dysfunction, persisting as long as 6 months or even years after the termination of treatment [2–4].

Through exploring the mechanism of OIPN, researchers have been trying to find potential prophylactic or therapeutic drugs all the time. Numerous clinical and preclinical studies have reported a series of effective agents for OIPN, such as calcium and magnesium injections [5], carbamazepine [6], oxcarbazepine [7], venlafaxine [8], gabapentin [9], pregabalin [10], glutathione [11], glutamine [12], alpha-lipoic acid [13], amifostine [14], Vitamin E [15], monosialoganglioside (GM1) [16], and novel agents such as niclosamide [17], fingolimod [18], N-acetylcysteine [19], milnacipran [20], riluzole [21], and a selective sigma-1 receptor antagonist MR309 [22]. Nonetheless, most studies either get negative results on further validation or remain at early stages, so that seldom drug has received recognition yet [1, 23]. According to the updated American Society of Clinical Oncology (ASCO) guideline, duloxetine is the only recommended treatment agent for patients with established painful OIPN. However, limited benefits and unfavorable side effects decrease the support of duloxetine [24, 25]. Besides, some of the nondrug treatment strategies, like exercise, scrambler therapy, cryotherapy, and compression therapy, are moderately recommended for further study for their potential benefits and reasonably safety but still lack strong evidence [26–28]. Therefore, seeking effective agents for OIPN is still an urgent and significant task.

According to the clinical characteristics, OIPN corresponds with “Bizheng” from the theory of traditional Chinese medicine (TCM), interpreted as arthromyodynia. Considering the hypoimmunity of patients receiving chemotherapy, deficiency of qi and meridian impassability are regarded as the vital pathogenesis of OIPN [29]. Yiqi-Wenjing-Fang (YWF) is a joint name of TCM prescriptions with similar effects of tonifying qi and warming meridians, represented by Huangqi Guizhi Wuwu decoction (HGWD) and Danggui Sini decoction (DSD), both from “Treatise on Cold Pathogenic and Miscellaneous Diseases.” Comparing the two representative prescriptions, HGWD is better at tonifying qi, while DSD is better at warming meridians. Our previous small-sample-size randomized controlled clinical trial (*n* = 72) showed that HGWD could effectively prevent OIPN through reducing the incidence and alleviating the symptoms of OIPN without affecting the chemotherapy efficacy [30]. Further mechanistic studies preliminarily revealed the correlation between HGWD and platinum transport and accumulation in dorsal root ganglion (DRG), as well as inflammatory responses, oxidative stress, axonal lesions, and neuronal and mitochondrial dysfunctions induced by platinum chelate [31, 32]. We conducted another randomized controlled clinical trial (*n* = 48) about DSD, which showed that DSD could significantly decrease the incidence and severity of acute OIPN [33]. Mechanistic studies demonstrated that the protective effects of DSD could be related to suppressing inflammatory lesions, improving ultramicrostructures, and enhancing amounts of Nissl bodies in DRG [34]. Although YWF has a strong clinical research basis in the efficacy and safety of OIPN prevention, further studies are necessary due to the insufficient sample size and the lack of placebo and parallel controls previously.

## 2. Method and Analysis

### 2.1. Objective

YWF have been empirically used to treat arthromyodynia for a long time in China, represented by HGWD and DSD, but there is a lack of evidence-based medical study. Small-sample-size clinical studies and animal experiments have been conducted and indicated positive efficacy of YWF granules on OIPN. To enlarge the sample size for further evaluation, 360 subjects for eligibility will be recruited. In addition, in order to compare the preventive efficacy on OIPN between HGWD granules and DSD granules, two paratactic treatment groups will be set according to the theory of treatment based on syndrome differentiation.

### 2.2. Study Design

This study is designed as a randomized, double-blind, placebo-controlled, and multicenter clinical trial that will last for 18 months from January 2021 to June 2022. It will be conducted in 30 clinical centers in China, and each center will have an investigator for enrolling the patients and collecting the data. The centers and their investigators are listed in Table 1.

The trial was registered at ClinicalTrials.gov (ID: NCT04690283), and the protocol version is 1.2/20200506. The flow chart is shown in Figure 1. The schedule of enrollment, interventions, and assessments is shown in Figure 2.

### 2.3. Eligibility Criteria

#### 2.3.1. Inclusion Criteria

Subject diagnosed with stage IIa-IIIc colorectal cancer, confirmed by histopathological examination, according to Chinese Society of Clinical Oncology (CSCO) guidelines for diagnosis and treatment of colorectal cancer.Subject suitable for receiving FOLFOX4 or mFOLFOX6 or XELOX as adjuvant chemotherapy after radical resection of colorectal cancer, receiving each dose and cumulative dose of oxaliplatin of 85 mg/m^2^ and ≥540 mg/m^2^, respectively.Subject with Karnofsky Performance Status Scale (Schag et al. 1984) index ≥60 points and an expected survival time ≥6 months.Subject aged between 18 and 80 years, men or women.Subject without severe damage of the heart, liver, kidney, or hematopoietic system.

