#### 2.3.2. Exclusion Criteria

Subject with any grade of peripheral neuropathy.Subject who has ever received treatment of neurotoxic chemotherapeutics, such as oxaliplatin, cisplatin, taxanes, or vinca alkaloids.Subject who is receiving agents with potential preventive or therapeutic effects to neuropathy, such as duloxetine, carbamazepine, venlafaxine, gabapentin, pregabalin, phenytoin, valproate, milnacipran, or tricyclic antidepressant.Subject who is participating or have participated in other clinical trials.Subject with a family history of hereditary/familial neuropathy.Subject who cannot take drugs orally.Subject with mental illness who cannot cooperate.Pregnant or lactation period women.

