#### 2.7.1. Primary Outcome

The degree of oxaliplatin-induced peripheral neuropathy will be evaluated according to the score of European Organization for Research and Treatment of Cancer Quality of Life Questionnaire-CIPN twenty-item scale (EORTC QLQ-CIPN20, 20–80 scores, with higher scores meaning a worse outcome), which is evaluated by the subject on 1 day before and 3 consecutive days after the first time of oxaliplatin administration. Subsequent assessments will be made every one time from cycle 2 to cycle 6, 1 month after the end of cycle 6, and then every 3 months up to 1 year.

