#### 2.7.2. Secondary Outcome

The grades of oxaliplatin-induced peripheral neuropathy will be evaluated according to the grades of National Cancer Institute-Common Terminology Criteria for Adverse Events Version 5.0 (NCI-CTCAE 5.0, 0–5 grades, with higher grade meaning a worse outcome), which is evaluated by the doctor on 1 day before the oxaliplatin administration from cycle 1 to cycle 6, 1 month after the end of cycle 6, and then every 3 months up to 1 year.QOL will be evaluated according to the score of European Organization for Research and Treatment of Cancer's Core Quality of Life Questionnaire (EORTC QLQ-C30, 28–112 scores, with higher scores meaning a worse outcome) on 1 day before the oxaliplatin administration from cycle 1 to cycle 6, 1 month after the end of cycle 6, and then every 3 months up to 1 year.Chemotherapeutic efficacy will be evaluated according to Response Evaluation Criteria in Solid Tumors Version 1.1 (RECIST 1.1) at the end of cycle 3 (and cycle 6 if it exists).The number of completed chemotherapy cycles will be recorded at the end of cycle 6 or after the last chemotherapy. If the result is less then 6, the specific reason should be noted.

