21	Yangzhou Hospital of Traditional Chinese Medicine	Yangzhou, Jiangsu Province	[name]
22	Zhejiang Provincial Hospital of Chinese Medicine	Hangzhou, Zhejiang Province	[name]
23	Hangzhou Hospital of Traditional Chinese Medicine	Hangzhou, Zhejiang Province	[name]
24	The First Affiliated Hospital of Guangxi University of Chinese Medicine	Nanning, Guangxi Province	[name]
25	Henan Cancer Hospital	Zhengzhou, Henan Province	[name]
26	Affiliated Hospital of Traditional Chinese Medicine of Southwest Medical University	Luzhou, Sichuan Province	[name]
27	Affiliated Hospital of Shanxi University of Traditional Chinese Medicine	Xianyang, Shanxi Province	[name]
28	Hunan Academy of Traditional Chinese Medicine Affiliated Hospital	Changsha, Hunan Province	[name]
29	Hebei General Hospital	Shijiazhuang, Hebei Province	[name]
30	The First Affiliated Hospital of Guizhou University of Chinese Medicine	Guiyang, Guizhou Province	[name]

*Note*. Each center was randomly assigned the center number, and the ranking had nothing to do with the center scale and the number of planned enrollment.

**Table 2 tab2:** Chemotherapy regimen.

Abbreviated name	Components	Dosage	Mode of administration	Treatment course
FOLFOX4	Oxaliplatin	85 mg/m^2^	Intravenous infusion for >2 hours on day 1	Every 2 weeks, at least 3 cycles
	Leucovorin	200 mg/m^2^	Intravenous infusion for >2 hours on days 1 and 2	
	5-Fluorouracil	400 mg/m^2^	Intravenous injection on days 1 and 2	
		600 mg/m^2^	Continuous intravenous infusion for 22 hours on days 1 and 2	

mFOLFOX6	Oxaliplatin	85 mg/m^2^	Intravenous infusion for >2 hours on day 1	Every 2 weeks, at least 3 cycles
	Leucovorin	400 mg/m^2^	Intravenous infusion for >2 hours on day 1	
	5-Fluorouracil	400 mg/m^2^	Intravenous injection on day 1	
		1200 mg/m^2^	Continuous intravenous infusion for 22 hours on days 1 and 2	

XELOX	Oxaliplatin	130 mg/m^2^	Intravenous infusion for >2 hours on day 1	Every 3 weeks, at least 4 cycles
	Capecitabine	1000 mg/m^2^	Oral administration twice a day on days 1–14	

**Table 3 tab3:** Standard formulation of YWF granules.

Huangqi Guizhi Wuwu decocion (HGWD) granules			
Pinyin name	English name	Latin name	Doses, g
Huangqi	*Astragalus membranaceus*	Astragali Radix Membranacei	18
Guizhi	Cassia twig	Ramulus Cinnamomi	9
Baishao	Radix Paeoniae Alba	Paeoniae Radix Alba	9
Shengjiang	Ginger	Rhizoma Zingiberis Recens	9
Dazao	Jujube	Fructus Zizyphi Jujubae	9

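### The oxaliplatin figures in the inclusion criterion conflict with Table 2: the XELOX dose differs from the stated per-dose figure, and every permitted minimum course falls short of the required cumulative dose

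*Protocol article*

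**What the plan says.** The second inclusion criterion (protocol article, section 2.3.1) opens with "Subject suitable for receiving FOLFOX4 or mFOLFOX6 or XELOX as adjuvant chemotherapy after radical resection of colorectal cancer" and continues in the same sentence with "receiving each dose and cumulative dose of oxaliplatin of 85 mg/m^2^ and ≥540 mg/m^2^, respectively". One pair of figures therefore covers all three regimens.

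Table 2 lists oxaliplatin on day 1 of each cycle:

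- FOLFOX4 and mFOLFOX6: 85 mg/m², "Every 2 weeks, at least 3 cycles".
- XELOX: 130 mg/m², "Every 3 weeks, at least 4 cycles".

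Section 2.3.2 excludes any "Subject who has ever received treatment of neurotoxic chemotherapeutics, such as oxaliplatin, cisplatin, taxanes, or vinca alkaloids".

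For the primary outcome, section 2.7.1 states: "Subsequent assessments will be made every one time from cycle 2 to cycle 6, 1 month after the end of cycle 6". Visits then follow every 3 months up to 1 year. Section 2.7.2 adds: "The number of completed chemotherapy cycles will be recorded at the end of cycle 6 or after the last chemotherapy". A reason must be noted if the count is below six.

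The Introduction links chronic neuropathy to about 3 months of repeated dosing, "usually with more than 540 mg/m^2^ cumulative dose of oxaliplatin". The same number appears as the cumulative figure in the criterion.

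**The concern.** An eligibility rule has to be decidable at each centre before a patient is randomised, and it has to agree with the treatment the protocol describes. This one does neither cleanly. Its per-dose figure fits two of the three regimens it names. Its cumulative figure exceeds what Table 2's shortest permitted course delivers under any of them.

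The practical risk is uneven application. With 30 centres, some could turn XELOX patients away, some could disregard the 85 mg/m² figure, and some could require a longer course than Table 2 does. The regimen mix and the oxaliplatin exposure of the enrolled population would then depend on how each centre read the sentence. Exposure matters here because the Introduction describes the neurotoxicity as dose-dependent.

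**Working it through.** **Inputs**

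- Required by section 2.3.1: 85 mg/m² at each dose; cumulative dose of at least 540 mg/m².
- Table 2: 85 mg/m² with a minimum of 3 cycles (FOLFOX4, mFOLFOX6); 130 mg/m² with a minimum of 4 cycles (XELOX); one oxaliplatin infusion per cycle.
- Oxaliplatin before entry: none (section 2.3.2).
- Last cycle in the cycle-based schedule: cycle 6 (section 2.7).

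**Formulas**

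- Cumulative dose = dose per cycle × number of cycles.
- Cycles needed = 540 ÷ dose per cycle, rounded up.

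**Per-dose check.** FOLFOX4 and mFOLFOX6: 85 = 85, met. XELOX: 130 ≠ 85, not met.

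**Cumulative check (mg/m²)**

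| | FOLFOX4 / mFOLFOX6 | XELOX |
|---|---|---|
| Minimum course | 3 × 85 = 255 | 4 × 130 = 520 |
| Shortfall against 540 | 285 (285/540 = 53%) | 20 (20/540 = 4%) |
| Six cycles | 6 × 85 = 510, short by 30 | 6 × 130 = 780, meets 540 |
| Cycles needed | 540/85 = 6.35, so 7 (595) | 540/130 = 4.15, so 5 (650) |

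The FOLFOX regimens need one cycle more than the cycle-based schedule covers. XELOX needs one cycle more than its stated minimum.

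**Other readings tried**

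- *The inequality also covers the per-dose figure.* XELOX would then pass the per-dose part. However, the text attaches the sign only to 540, and the cumulative shortfalls would remain.
- *XELOX given at the criterion's 85 mg/m².* Four cycles give 340 and six give 510, both below 540.
- *A FOLFOX cycle of 4 weeks with two infusions, which is not what Table 2 says.* Three cycles would give 3 × 2 × 85 = 510, still short; six would give 1,020.

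None of these readings makes section 2.3.1 and Table 2 agree in full.

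**The case against.** The best defence is that the intent can be inferred. XELOX is named as eligible and Table 2 gives its dose, so the sponsor plainly means to enrol those patients. Table 2 sets a minimum number of cycles and no maximum, so a patient whose planned course is longer can satisfy the cumulative figure; for XELOX one further cycle is enough. Nothing says chemotherapy ends at cycle 6, and follow-up runs to 1 year, so observation does not stop at 510 mg/m². The Introduction's 540 is described as usual and is not presented as a level to be reached within six cycles.

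Most of this stands. It reduces the six-cycle point to a tension. It does not remove the per-dose mismatch, nor the fact that Table 2 permits courses that cannot satisfy the criterion.

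Two stronger readings are tempting, and the documents do not support either.

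- *Patients who stop early would become ineligible after randomisation, so that the trial selects on a consequence of treatment.* The clause sits under suitability for a regimen, which points to intended exposure. No section removes a randomised patient for a low cumulative dose, and the termination criteria in section 2.3.3 contain no such rule. Section 2.7.2 expects short courses and records them.
- *The visit one month after cycle 6 should be tied to the last oxaliplatin dose instead.* If FOLFOX continued to a seventh cycle on the 2-week schedule, that visit would fall after further oxaliplatin. But the article does not call it a post-treatment visit. Tying it to the last dose would also make its timing depend on an event after randomisation that neuropathy can change. That is a debatable trade-off and not a correction.

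**Conclusion.** The inclusion criterion is wrong as written and needs reconciling with Table 2. The per-dose conflict is complete on the literal text: 85 mg/m² is required and XELOX is listed at 130 mg/m², so every XELOX patient treated per Table 2 fails. The cumulative conflict affects all three regimens at their permitted minimum, by 285 mg/m² for the FOLFOX regimens and 20 mg/m² for XELOX. The six-cycle FOLFOX shortfall of 30 mg/m² is a lesser tension between the criterion and the assessment schedule.

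These conclusions assume one oxaliplatin infusion per cycle at the Table 2 dose, no dose reduction, and no earlier exposure, all as the article states or as the full scheduled dose implies. The consequence is ambiguity about who may enter and on what planned exposure. The document does not show that anyone would be removed from the analysis.

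**What to change.** Reconcile section 2.3.1, sections 2.7.1 and 2.7.2, and Table 2, so that the per-dose figures, the minimum courses, the cumulative figure and the cycle-based schedule agree. Which figures stand is for the clinical team to decide. In the revised criterion:

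- state the per-dose oxaliplatin figure separately for each regimen;
- word the cumulative figure explicitly as the dose planned at enrolment, so that it can be checked before randomisation and applied uniformly across the 30 centres;
- make clear how that planned dose relates to the minimum number of cycles in Table 2 and to the six cycles used in section 2.7.

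The cost is a protocol wording amendment and a notice to centres. No additional patients, visits or procedures are needed.

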#### 2.3.2. Exclusion Criteria

Subject with any grade of peripheral neuropathy.Subject who has ever received treatment of neurotoxic chemotherapeutics, such as oxaliplatin, cisplatin, taxanes, or vinca alkaloids.Subject who is receiving agents with potential preventive or therapeutic effects to neuropathy, such as duloxetine, carbamazepine, venlafaxine, gabapentin, pregabalin, phenytoin, valproate, milnacipran, or tricyclic antidepressant.Subject who is participating or have participated in other clinical trials.Subject with a family history of hereditary/familial neuropathy.Subject who cannot take drugs orally.Subject with mental illness who cannot cooperate.Pregnant or lactation period women.

#### 2.3.3. Termination Criteria

Subject withdraws from informed consent.Disease progression of subject is confirmed by imageological examination or clinical assessment.Subject experienced adverse events that the investigator deemed necessary to terminate trial treatment.Subject experienced severe side effects that the investigator deemed necessary to terminate trial treatment.Subject who stops or discontinues their medication without authorization.Subject who is less compliant with trial regulations intentionally or unintentionally.Other circumstances that may be detrimental to subject.

### 2.4. Sample Size Calculation

This study is suitable for superiority test. Although without positive-control group, the method of sample size calculation is equal to the three-arm trial. Based on the incidence of OIPN, the incidence of the placebo-control group was assumed as 40%, and the incidences of two intervention groups were both assumed as 20%. The Pearson chi-square test was used to calculate the appropriate sample size for each group. Taking the 20% shedding rate into account and rounding off, each group needs 120 samples and a total of 360 samples.

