### 2.10. Statistical Analysis

This study cooperates with Statistics Department of Nanjing University of Traditional Chinese Medicine. After the test trial is determined, a special statistician will be employed for making the statistical analysis plan. All data will be statistically analyzed by SAS 9.3 software. Enumeration data will be expressed as percentage, while measurement data will be expressed as mean ± standard deviation. For comparison of count or grade data, chi-square test will be used. Two logistic multiple regressions (Enter method) will be used to analyze the factors affecting the objective curative effect.

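### The 120 per arm is justified on an undefined yes/no incidence of OIPN, while the primary outcome is the QLQ-CIPN20 score, so the stated size is not justified for the primary outcome

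*Protocol article*

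**What the plan says.** **Sample size (section 2.4).** The calculation rests on a proportion of patients with OIPN: "Based on the incidence of OIPN, the incidence of the placebo-control group was assumed as 40" per cent, and "the incidences of two intervention groups were both assumed as 20" per cent. The method is named: "The Pearson chi-square test was used to calculate the appropriate sample size for each group". The result is: "Taking the 20% shedding rate into account and rounding off, each group needs 120 samples and a total of 360 samples". Nothing in the section says what makes a patient a case, on which scale, or by when.

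**Primary outcome (section 2.7.1, and the Abstract).** "The degree of oxaliplatin-induced peripheral neuropathy will be evaluated according to the score of European Organization for Research and Treatment of Cancer", followed by the name of the CIPN20 module and its range of 20 to 80. The patient completes it the day before and on three days after the first oxaliplatin dose, then at cycles 2 to 6, one month after cycle 6, and every three months up to one year. No visit is singled out and no score marks a case.

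**Secondary outcome (section 2.7.2).** The NCI-CTCAE grade, which could more naturally yield an incidence, is secondary. It too has no grade threshold.

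**Analysis (section 2.10).** "while measurement data will be expressed as mean ± standard deviation. For comparison of count or grade data, chi-square test will be used". A logistic regression is planned for factors related to curative effect, a term not tied to the CIPN20 score. The section says that a statistician will write the analysis plan later.

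**The concern.** A sample size calculation shows that the trial can answer its primary question. Here it concerns a different quantity, and one that the article does not define. The sizing and the only named between-group test both suit categorical data, while the declared primary outcome is a score.

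Two things are at stake. First, a reader cannot tell whether success means a lower score or fewer cases. If it means cases, the cut-off and visit could still be chosen after data are seen. Second, a null or positive result on the score cannot be set against any planned effect, because no difference or SD on that scale was planned.

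**Working it through.** **Inputs from section 2.4:** 40% (placebo), 20% (each active arm), 20% loss, 120 per arm. Significance level, sidedness and power are not given there, so conventional values are assumed below.

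**Step 1. Can 120 be reproduced for the binary endpoint?** Two arms, pooled variance, mean proportion 0.30:

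n = [z(α/2)·√(2·0.30·0.70) + z(β)·√(0.40·0.60 + 0.20·0.80)]² / 0.20²

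where √0.42 = 0.648 and √0.40 = 0.632. Each n is divided by 0.80 for loss.

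| Assumed method | n evaluable | n per arm after loss |
|---|---|---|
| Pooled, two-sided 0.05, 80% power | 82 | 103 |
| Pooled, two-sided 0.05, 85% power | 93 | 117 |
| Pooled, two-sided 0.05, 90% power | 109 | 137 |
| Unpooled, two-sided 0.025, 80% power | 96 | 120 |
| Three-arm chi-square (2 df), 0.05, 90% power | 93 | 117 |

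Several ordinary choices land on 117 to 120, so the binary figure is plausible. Without the significance level and power it cannot be pinned to one calculation.

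**Step 2. Power for the binary endpoint with 120 × 0.80 = 96 evaluable per arm.**

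Two-sided 0.05: (0.20·√96 − 1.960·0.648)/0.632 = (1.960 − 1.270)/0.632 = 1.09, power 86%.

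Two-sided 0.025 (two comparisons with placebo): (1.960 − 2.241·0.648)/0.632 = 0.80, power 79%.

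The three-arm test at 0.05 has 91%.

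**Step 3. What the same 96 per arm gives on the score.** No CIPN20 difference or SD is stated, so the result can be given only in SD units. The standard error of a difference is √(2/96) = 0.1443 SD.

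- 80% power at two-sided 0.05: (1.960 + 0.842)·0.1443 = 0.40 SD.
- 80% power at two-sided 0.025: (2.241 + 0.842)·0.1443 = 0.445 SD.

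Power at two-sided 0.05 is Φ(d/0.1443 − 1.960). The size needed for 80% power is 2·(1.960 + 0.842)²/d², divided by 0.80.

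| Assumed true difference d (SD) | Power with 96 per arm | Per arm needed for 80%, after loss |
|---|---|---|
| 0.2 | 28% | 492 |
| 0.3 | 55% | 219 |
| 0.4 | 79% | 124 |
| 0.5 | 93% | 79 |

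The same 120 per arm is ample at 0.5 SD, about right at 0.4 and inadequate at 0.3 or below. The article gives nothing that selects a row.

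**The case against.** **The size may well be adequate.** If the score were normal with equal SDs, 40% versus 20% above a cut-off would imply a shift of 0.842 − 0.253 = 0.59 SD. With 96 per arm, power on the score would then be about 98% at 0.05 and 97% at 0.025. This stands as a reason not to call the trial too small. It does not supply the justification: the article does not say that its incidence is a cut of the CIPN20 score, and it gives no distribution for that score.

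**The analysis plan is still to come.** Section 2.10 says so, and a condensed article may leave the test for a score to that plan. This also stands. A reader might infer that the score will never be tested, or will be dichotomised afterwards. The text does not show either, because the later plan can name a test. The chi-square sentence only corroborates the mismatch. A later plan cannot, however, make the calculation stated in section 2.4 apply to a different outcome.

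**The 40% might seem contradicted by the Introduction.** That section says "About 90% of patients will undergo acute OIPN symptoms", and the first scores fall in the days after the first infusion. A reader might conclude that 40% is wrong and that power is much lower than planned. The documents do not support this. The Introduction's figure concerns acute symptoms only. Section 2.4 does not say that its incidence is acute, and follow-up runs to one year, into the period of chronic OIPN. An undefined rate cannot be shown to conflict with a defined one.

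**Conclusion.** The concern holds as a mismatch between sections 2.4 and 2.7.1: the stated 120 per arm was derived for an undefined binary event and is not justified for the repeated CIPN20 score that is the primary outcome. The binary arithmetic is not in dispute.

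It would go too far to say that the trial is underpowered for its primary question. Power on the score at two-sided 0.05 runs from 28% to 93% as the true difference goes from 0.2 to 0.5 SD, and the article does not say where in that range the sponsor expects to be. These figures assume two-group comparisons of means, 96 evaluable per arm and no gain from baseline adjustment. No such gain is counted because no correlation is given. In addition, section 2.3.2 excludes patients with any neuropathy, so baseline scores probably cluster near the minimum.

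**What to change.** 1. In section 2.7.1, name one primary quantity: the QLQ-CIPN20 score at one stated visit, each active arm versus placebo. The other visits become supporting.
2. In section 2.10, name the comparison: ANCOVA or a repeated-measures model, adjusted for the score taken before the first oxaliplatin dose.
3. In section 2.4, restate the size in score units. The sponsor states the SD and relevant difference it assumes, the significance level for the two comparisons with placebo, and the power that 96 evaluable per arm then provides.
4. Keep incidence as a secondary outcome with instrument, grade and time window fixed.

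An equally valid repair is to define incidence by instrument, cut-off and time window, and make it the primary outcome. Section 2.4 would then apply once the 40% and 20% are tied to that definition.

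Either route is a change of wording in these sections, to be made before unblinding. It needs no new visits or data, since the baseline score is already collected. Aligning the text needs no more patients, but that holds for the trial only if the stated difference is one that 120 per arm can detect. At 0.3 SD, for example, 219 per arm would be needed.
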